### Data collection

Data collection in the patient trial group will be conducted via an eCRF by designated ICU staff, weaning centres and the study centre using Redcap (Research Electronic Data Capture). The data of the comparison group is generated from AOK-BW health care claims data, delivered to the aQua Institute (Institute for Applied Quality Promotion and Research in Health Care) and processed there and analysed in the IMBI (Institute of Medical Biometry and Informatics). Data from the e-learning will be evaluated via the Moodle platform, the central learning platform of the University of Heidelberg. Publicity is recorded on the basis of visits/clicks, which is provided by the respective platforms. More detailed information can be found in the Supplement.

### Sample size

For the purpose of power estimation, we assumed that 1,495 high-risk patients per group would be recruited. Further, we assumed patients are recruited in 40 cooperating ICU with an average cluster size of 25 and an intra-class correlation coefficient of 0.1, yielding a design effect coefficient of 3.4 [32]. Incorporating this into our power calculation would give us an effective sample size of 439 in both groups. Presuming a drop-out rate of 10.6%, we would reach an effective sample size of 393 in both groups. Assuming a rate of 20% weaning failures in the intervention and 30% in the comparison group, a chi-squared test with a significance level of 5% would have a power of 90% to detect a difference between the treatment and the comparison group. The actual primary analysis will be based on a mixed logistic regression model adjusted for various confounders including correlations within clusters, which can be expected to have better operating characteristics than a chi-squared test. This power analysis was conducted using PASS version 16.0.3.

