**Methods:**

The PRiVENT intervention is a prospective, mixed-methods interventional, multicentre study with a parallel comparison group selected from insurance claims data of the health insurer Allgemeine Ortskrankenkasse Baden-Württemberg (AOK-BW) conducted in Baden-Württemberg, Germany, over 24 months. Four weaning centres supervise 40 intensive care units (ICUs), that are responsible for patient recruitment. The primary outcome, successful weaning from IMV, will be evaluated using a mixed logistic regression model. Secondary outcomes will be evaluated using mixed regression models.

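### The sample-size inputs conflict (40 ICUs of 25 patients is 1,000, not 1,495 per group), so the 90% power is not supported as written

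*Protocol article*

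**What the plan says.** All the planning inputs stand in one paragraph, under Sample size. It opens with the group size: "we assumed that 1,495 high-risk patients per group would be recruited". It then gives the clustering assumptions: "we assumed patients are recruited in 40 cooperating ICU with an average cluster size of 25 and an intra-class correlation coefficient of 0.1". From these it takes a design effect of 3.4, which "would give us an effective sample size of 439 in both groups". A drop-out rate of 10.6% brings this to 393 per group. For failure rates of 20% and 30%, a chi-squared test at the 5% level is said to have 90% power. The paragraph adds that the actual analysis will use an adjusted mixed logistic model, "which can be expected to have better operating characteristics than a chi-squared test".

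The number 40 is not confined to this paragraph. The Abstract states: "Four weaning centres supervise 40 intensive care units (ICUs), that are responsible for patient recruitment". The Study design section repeats 40 ICUs. The section on the comparison group draws those patients from insurance claims of hospitals in Baden-Württemberg and does not say how many hospitals.

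**The concern.** Number of clusters, mean cluster size and total are tied by simple multiplication, and here the product fails: 40 × 25 = 1,000, not 1,495. The calculation divides the larger total (1,495) by the design effect of the smaller clusters (25). Both choices raise the effective sample size, so the error runs in the favourable direction.

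This paragraph is the article's only power justification for the primary outcome. If the power is lower than stated, a non-significant result carries a higher chance of a missed effect than the stated 10%, and readers would have no way of knowing it.

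**Working it through.** **Inputs (all from Sample size):** N = 1,495 per group; K = 40 ICUs; m = 25 per ICU; ICC = 0.1; drop-out 10.6%; failure rates 0.20 and 0.30; 5% level. Sidedness is not stated; a two-sided test reproduces the stated power.

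**Formulas.** Design effect DE = 1 + (m − 1) × ICC. Effective size = N / DE. Power is the normal approximation for two proportions with pooled variance under the null.

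**1. The stated figure reproduces.**
- DE = 1 + 24 × 0.1 = 3.4
- 1,495 / 3.4 = 439.7
- 439.7 × 0.894 = 393.1
- Power with 393 per group = 90.1%

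The steps are carried out correctly. The problem lies in the inputs.

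**2. The inputs are inconsistent.**
- 40 × 25 = 1,000
- 1,495 / 25 = 59.8, so about 60 ICUs would be needed at 25 each
- 1,495 / 40 = 37.4 per ICU
- Drop-out does not close the gap: 1,495 × 0.894 = 1,337, and 1,337 / 40 = 33.4 per ICU

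**3. Ceiling for 40 clusters.** Effective size is Km / (1 + (m − 1) × ICC). As m grows this approaches K / ICC = 40 / 0.1 = 400. An effective 439 is therefore out of reach for a group recruited in 40 ICUs, whatever the cluster size. An effective 393 would need m = 393 × 0.9 / (40 − 39.3) ≈ 505 patients per ICU.

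**4. Power on consistent inputs.** In the article's own order, with drop-out after clustering: DE = 1 + 36.375 × 0.1 = 4.64; 1,495 / 4.64 = 322; × 0.894 = 288. With drop-out first: DE = 1 + 32.4 × 0.1 = 4.24; 1,337 / 4.24 = 315.

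| Reading | Effective size, intervention / comparison | Power |
|---|---|---|
| As stated | 393 / 393 | 90.1% |
| 1,495 in 40 clusters, both groups, drop-out after clustering | 288 / 288 | 79.3% |
| Same, drop-out before clustering | 315 / 315 | 82.8% |
| 1,495 in 40 ICUs for intervention only; comparison keeps 393 | 288 / 393 | 84.5% |
| Same, drop-out first in the intervention group | 315 / 393 | 86.3% |
| 40 × 25 = 1,000 per group, DE 3.4, drop-out after | 263 / 263 | 75.6% |

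**5. Sensitivity to the number of comparison hospitals.** This number is assumed, because the article gives none. There are 1,495 per group, the intervention group is in 40 ICUs, and the ICC is 0.1 in both groups.

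| Comparison hospitals | Power, drop-out after clustering | Power, drop-out before clustering |
|---|---|---|
| 40 | 79% | 83% |
| 60 | 85% | 87% |
| 80 | 87% | 90% |
| 100 | 89% | 91% |

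**6. Detectable difference.** With 40 clusters in both groups, 90% power against a 30% comparison rate needs an intervention rate of about 18.5% (effective 288) to 19% (effective 315), instead of 20%.

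**7. What would restore 90%.** About 60 ICUs of 25 patients would do so. So would an ICC of 2.4 / 36.375 ≈ 0.066 at 37.4 per ICU, since that brings the design effect back to 3.4.

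**The case against.** The strongest reply is that 79% is not established either. It puts the comparison group in 40 clusters of 37.4, but the 40 refers to the cooperating ICUs, which are the intervention sites. The comparison patients come from claims of an unstated number of hospitals. With 80 to 100 of them, power is about 87% to 91% with no change to enrolment. Nor do the documents show which of 1,495, 40 or 25 is wrong. This stands. A reader might infer that the design delivers 79% power and has twice the stated type II error. That is one reading among several, and the documents do not fix it. For the same reason the ceiling of 400 applies to the intervention group and not necessarily to the comparison group.

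It could also be said that the mixed model will make up the difference. The article puts no number on that remark. The 393 is already deflated for clustering, so modelling the clustering is not a further gain over it. Covariate adjustment could help through prognostic covariates or cost precision where covariates are associated with treatment group in a non-randomised comparison. The net effect cannot be determined from the documents. A reader might want the sentence struck out as false, but the documents do not support going that far. They support only that it cannot be relied on to cover the gap.

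Finally, the error leaves the primary model, the analysis population and the validity of the estimate untouched. That is true, and it limits the point to the power statement.

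**Conclusion.** The point holds as an arithmetic contradiction. The figures 1,495, 40 and 25 cannot all be true, the effective size of 439 is unattainable for the intervention group under the stated ICC, and the 90% rests on the mismatch.

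The size depends on how it is resolved. It is about 79% to 83% with 40 clusters in both groups, about 84% to 86% if the comparison group keeps an effective 393, and about 76% with 1,000 per group. Power is near 90% only if the comparison group spans roughly 80 or more hospitals, which is an assumption. All these figures take equal cluster sizes within a group, an ICC of 0.1 in both groups, and a two-sided 5% test.

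**What to change.** Rewrite the sample-size paragraph:

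- Reconcile the total per group, the number of ICUs and the mean cluster size, and say which of the three was in error.
- State the number of hospitals and mean cluster size assumed for the claims-based comparison group.
- Compute the design effect separately for each group, and say whether drop-out is removed before or after it.
- Restate the power for 20% versus 30%, with a range over the number of comparison hospitals if that is not yet known. Alternatively, state the difference detectable at 90% power.
- Do not rely on the mixed-model remark to cover any shortfall unless its effect on power is quantified.

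The cost is a corrected paragraph and probably a less favourable power figure. No added enrolment is needed.

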#### Comparison group of the intervention study

The comparison group will be matched from AOK-BW health care claims data provided by hospitals in Baden-Württemberg. Because of the necessary processing in AOK-BW the data will be available from late 2019 to late 2023. Only patients ventilated for at least 96 h will be included in the comparison group. Patient data will then be reviewed for the other eligibility criteria and the risk of long-term IMV will be assessed by the prognostic model. Patients admitted to the hospital with acute COVID-19 pneumonia are automatically classified as high-risk. The group of patients used for the primary assessment of the intervention effect will be additionally limited to patients who do not die within 11 days of starting ventilation. This ensures comparability with the intervention group and corresponds to the screening period in the intervention group.

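### The power calculation gives the claims-based comparison group the clustering and drop-out of the 40 cooperating ICUs, so that group's effective size, and the 90% power, have no valid basis

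*Protocol article*

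**What the plan says.** The Sample size section starts from equal groups: "we assumed that 1,495 high-risk patients per group would be recruited". It then describes the clustering: "patients are recruited in 40 cooperating ICU with an average cluster size of 25 and an intra-class correlation coefficient of 0.1". From these three values it takes a design effect of 3.4. The result is applied to both groups without distinction: "Incorporating this into our power calculation would give us an effective sample size of 439 in both groups". Drop-out is treated in the same way: "Presuming a drop-out rate of 10.6%, we would reach an effective sample size of 393 in both groups". The failure rates are 20% and 30%, and a chi-squared test at the 5% level is said to have 90% power.

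The comparison group has a different origin. Under Comparison group of the intervention study: "The comparison group will be matched from AOK-BW health care claims data provided by hospitals in Baden-Württemberg". According to Recruitment of patients, only the experimental group comes from PRiVENT ICUs. The document gives no number of comparison hospitals, no comparison cluster size, and no reason why claims patients would drop out.

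**The concern.** The design effect 1 + (m − 1) × ICC depends on the number of patients per cluster, m. The value m = 25 describes recruitment in cooperating ICUs. For the claims group, m is set by how many hospitals supply the comparators, which is a different and unstated quantity. At an ICC of 0.1 that number largely determines the group's effective size.

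The drop-out rate is also a feature of enrolment. Comparators are selected from existing records. Under Outcomes, death before weaning, continued ventilation at discharge and non-discharge by the cut-off all count as failures, so they are not lost observations.

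At stake is whether the stated 90% power describes the comparison that will be made.

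**Working it through.** **Inputs, all from the Sample size section:** 1,495 per group; 40 ICUs; cluster size 25; ICC 0.1; drop-out 10.6%; failure rates 0.20 and 0.30; alpha 5%. Sidedness is not stated. Two-sided without continuity correction is assumed, because it reproduces the stated power.

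**Step 1. Reproduce the plan.**
- Design effect: 1 + (25 − 1) × 0.1 = 3.4.
- Effective size: 1,495 / 3.4 = 439.7. After drop-out: 439.7 × (1 − 0.106) = 393.1.
- Power = Φ{[0.10 − 1.96 × SE0] / SE1}, where SE0 uses the pooled rate and SE1 the separate rates. With 393 per group, SE0 = √(0.25 × 0.75 × 2/393) = 0.03089 and SE1 = √((0.16 + 0.21)/393) = 0.03068. This gives Φ(1.286) = 90.1%.

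The stated chain is arithmetically correct.

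**Step 2. Remove drop-out from the comparison group only.** With 393 against 439, power is 91.5%. On its own, the carried-over drop-out is slightly conservative.

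**Step 3. Give the comparison group its own clustering.** For H hospitals, m = 1,495 / H, design effect = 1 + (m − 1) × 0.1, and effective size = 1,495 / design effect, with no drop-out. The intervention group stays at 393. H is an assumption, so a range is shown.

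| Assumed hospitals H | m | Design effect | Effective comparators | Power |
|---|---|---|---|---|
| 40 | 37.38 | 4.64 | 322 | 87.0% |
| 60 | 24.92 | 3.39 | 441 | 91.6% |
| 80 | 18.69 | 2.77 | 540 | 93.7% |
| 100 | 14.95 | 2.40 | 624 | 94.9% |
| 150 | 9.97 | 1.90 | 788 | 96.3% |

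For example, at H = 40 the pooled rate is (393 × 0.2 + 322 × 0.3)/715 = 0.245, SE0 = 0.03233, SE1 = √(0.16/393 + 0.21/322) = 0.03255, and power = Φ(1.126) = 87.0%.

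**Step 4. Break-even points.** The plan's 439 needs 1,495 / 25 = 59.8, so about 60 hospitals. For 90% power without comparator drop-out, 393 effective comparators suffice. The design effect is then 1,495 / 393 = 3.80, m = 1 + 2.80/0.1 = 29, and 1,495 / 29 is about 52 hospitals. Neither count appears in the protocol.

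**Step 5. Would a larger comparison group help?** Doubling to 2,990 within the same hospitals also doubles m. Power moves from 87.0 to 88.7% (40 hospitals), 91.6 to 93.1% (60) and 94.9 to 96.2% (100). With H fixed, the effective size cannot exceed H / ICC, which is 400 for 40 hospitals. Material gains come from more hospitals rather than from more patients per hospital.

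**The case against.** The strongest reply is that this is a planning assumption, that its arithmetic is right, and that no harm is shown. Much of that stands. The drop-out assumption errs on the safe side, four of the five hospital scenarios stay above 90%, and the lowest is 87%. The Analysis section also plans an adjusted mixed model with a centre random intercept, so clustering will be handled in the analysis whatever the planning figure says. What the reply does not supply is a basis for 439 or 393 in the comparison group.

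Three stronger readings are tempting, and the document does not support them.
- *The comparison group is capped at 1,495.* That figure is introduced as an assumption for power estimation. No maximum or matching ratio is fixed, and a ratio may properly be left to the analysis plan.
- *The comparators come from other hospitals.* The text says only hospitals in Baden-Württemberg. Non-overlap with PRiVENT ICUs is plausible, because staff training acts at ICU level, but it is an inference. Overlap would not rescue the figure: the contrast would then be partly within centre, and inflating each group independently would not give the right variance.
- *Enlarging the group is free power.* The pool is limited to one insurer, the eligibility criteria, the high-risk class, survival beyond 11 days and matching. Nothing shows that more than 1,495 eligible patients exist, and Step 5 shows a small gain within a fixed number of hospitals.

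**Conclusion.** The point holds for the comparison group. Its design effect and drop-out are taken from a recruitment process that it does not go through, so its effective size, and with it the 90% power, is not established. Over an assumed 40 to 150 hospitals, power is 87 to 96%, against 90.1% as planned. The sign of the error is unknown, and a reader should not conclude that the trial is underpowered on this account.

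The range rests on these assumptions: an ICC of 0.1 in the claims hospitals, equal cluster sizes, clusters that do not overlap between groups, a two-sided uncorrected test, and an intervention group at its stated 393. The last is taken as given. The section's 40 ICUs of 25 make 1,000 rather than 1,495, but that is a separate question about the intervention group and is not used here.

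This is a correction worth making to a figure the trial relies on. It does not threaten the design.

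**What to change.** In Sample size, compute the effective size separately for each group. Use the cooperating ICUs with drop-out for the intervention group. Use the actual number of contributing claims hospitals, without recruitment drop-out, for the comparison group. Restate the power, or give its range if the hospital count is not yet known. State whether hospitals with PRiVENT ICUs can supply comparators, because the variance formula depends on it.

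In Comparison group of the intervention study, add a sentence that all eligible high-risk claims patients may be used, through variable-ratio matching or weighting, so that equal group sizes need not be assumed.

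The cost is a hospital count from the claims holder, a short recalculation, and more claims records to process. No additional recruitment is needed. The expected gain from more comparators is modest, about 1 to 2 percentage points for a doubling, unless more hospitals contribute.

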### Analysis

#### Interim analysis

There will be an interim analysis after 12 months of intervention and a final analysis at the end of the entire intervention period. The aim of the interim analysis is to assess the recruitment effort of the centres and the influence of COVID-19 on the outcomes. The results are accessible to the PRiVENT study group.

#### Final analysis

The primary outcome, successful weaning before discharge, will be evaluated using a mixed logistic regression model including treatment group, age, gender, acute COVID-19 pneumonia, pre-existing medical conditions via the Charlson Comorbidity Index (continuously) [33], number of ventilation cases of the centre, dependency on ventilatory assistance for at least 3 month within 1 year before admission (with tracheostomy vs without tracheostomy vs none), tracheostomy within 96 h of intubation, extracorporeal support (yes/no), and centre as a random intercept. The analysis population for the primary endpoint will be restricted in order that a possible bias due to the selection effect of the screening window will be minimized. If necessary, missing values will be imputed via a multiple imputation approach. For patients included into the analysis population, intercurrent events (such as death) which would prevent patients’ successful weaning will be counted as weaning failures. A number of sensitivity analysis will be conducted to investigate the impact of the imputation strategy, the 7-day inclusion window, and the choice of covariates.

The analysis of secondary outcomes will include the calculation of appropriate summary measures of the respective empirical distributions (mean, standard deviation, median, interquartile range, minimum and maximum for continuous variables, and absolute and relative frequencies for categorical variables), as well as descriptive *p*-values. In addition, similar mixed models as described for the primary outcome will be used, logistic models for categorical outcomes and linear models for continuous outcomes. Time to event endpoints will be analysed using methods from survival analysis, including Kaplan–Meier estimates, log-rank tests and shared frailty models similar to the primary analysis model. As appropriate, graphical methods will be used to visualise the results. Missing data in secondary outcomes will not be imputed.

In an explorative analysis, clinical data collected within the trial will be used in to identify potentially relevant factors which could help to supplement the developed prognosis model. To this end, an elastic-net approach, as well as decision-tree based models will be used.

A detailed statistical analysis plan will be set up prior to the final analysis. R version 4.0.2 or higher (www.R-project.org) will be used to carry out the analyses.

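### The planned log-rank tests ignore the ICU clustering that the protocol itself assumes; time-to-event p-values should come from the shared frailty model planned beside them

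*Protocol article*

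**What the plan says.** All references are to the protocol article.

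- **Final analysis, time-to-event endpoints:** "Time to event endpoints will be analysed using methods from survival analysis, including Kaplan–Meier estimates, log-rank tests and shared frailty models". The sentence goes on to liken the frailty models to the primary model, which has a random intercept for centre. No stratification, robust variance or other cluster adjustment is stated for the log-rank test.
- **Final analysis, other secondary outcomes:** summary measures are planned, "as well as descriptive *p*-values. In addition, similar mixed models as described for the primary outcome will be used". The test behind the descriptive p-values is not named.
- **Sample size:** the power calculation assumes an "average cluster size of 25 and an intra-class correlation coefficient of 0.1, yielding a design effect coefficient of 3.4".
- **Recruitment of patients:** the experimental group comes from participating ICUs. The comparison group comes from insurance claims of hospitals in the state, and the number and size of its clusters are not given.
- **Study design and Intervention elements:** the intervention works at several levels. Staff training, quality circles and e-learning are delivered to the ICU; weaning boards and consults concern the individual patient.

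**The concern.** The plan treats outcomes within an ICU as correlated and builds this into both the power calculation and the primary model. The ordinary log-rank test does not. Where group membership largely follows the ICU, between-hospital variation enters the group contrast, and a test that ignores it uses too small a variance.

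At stake is the reading of endpoints such as time from intubation to successful weaning, and of mortality if it is analysed as time to event. A small log-rank p-value beside a Kaplan-Meier plot could reflect ordinary differences between hospitals, and it could disagree with the frailty model for the same endpoint. In a non-randomised study the log-rank test has a second weakness: unlike the models, it does not adjust for confounders.

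**Working it through.** **1. Reproduce the plan's own figures (Sample size section).** Inputs: 1,495 per group, mean cluster size 25, ICC 0.1, drop-out 10.6%, weaning failure 20% vs 30%, 5% level (taken as two-sided).

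- Design effect: DE = 1 + (m − 1) × ICC = 1 + 24 × 0.1 = 3.4.
- Effective n: 1,495 / 3.4 = 439.7; × (1 − 0.106) = 393.1.
- Power at 393 per group, pooled test without continuity correction: null standard error √(2 × 0.25 × 0.75 / 393) = 0.0309; alternative standard error √((0.16 + 0.21) / 393) = 0.0307; Φ((0.1 − 1.96 × 0.0309) / 0.0307) = 0.901.

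The stated 3.4, 439, 393 and 90% all reproduce.

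**2. True size of a test that ignores clusters.** With clusters nested in group, the real variance is DE times the variance used, so a nominal 5% test rejects under no effect with probability 2 × (1 − Φ(1.96 / √DE)).

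- m = 25: DE 3.4; 1.96 / √3.4 = 1.063; size 28.8%.
- m = 37.4: DE 1 + 36.4 × 0.1 = 4.64; 1.96 / √4.64 = 0.910; size 36.3%.

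The second case is shown because "we assumed that 1,495 high-risk patients per group would be recruited" and 1,495 / 40 ICUs = 37.4, whereas 40 × 25 is only 1,000.

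**3. Does the formula carry over to the log-rank test?** Simulation with no treatment effect: 40 clusters per group, exponential event times, log-normal cluster frailty calibrated so that event status by the end of follow-up has ICC 0.1, 2,000 runs per setting.

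| Proportion with event | 25 per cluster | 37 per cluster |
|---|---|---|
| 75% | 32.1% | 38.1% |
| 30% | 29.3% | 38.0% |

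The simulated sizes are close to the formula and slightly above it.

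**4. Sensitivity to what the article does not give.**

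*ICC of the time-to-event endpoints, both groups clustered alike:*

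| ICC | m = 25 | m = 37.4 |
|---|---|---|
| 0.01 | 7.8% | 9.3% |
| 0.05 | 18.6% | 24.3% |
| 0.1 | 28.8% | 36.3% |

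*Comparison patients spread over many hospitals (ICC 0.1, equal group sizes, DE averaged over the two groups):*

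- 25 per intervention ICU and 1 per comparison hospital: DE (3.4 + 1) / 2 = 2.2, size 18.6%. With 15 per comparison hospital: DE (3.4 + 2.4) / 2 = 2.9, size 25.0%.
- 37.4 per intervention ICU and 1 per comparison hospital: DE (4.64 + 1) / 2 = 2.82, size 24.3%. With 15: DE (4.64 + 2.4) / 2 = 3.52, size 29.6%.

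*The same hospitals supplying both groups equally:* hospital effects cancel, DE = 1 − 0.1 = 0.9, size 3.9%.

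**The case against.** The strongest reply is that the plan already contains the remedy. The same sentence provides shared frailty models like the primary model, and the other secondary outcomes get mixed models. The secondary p-values are called descriptive, the 5% level appears only in the power calculation for the primary outcome, and a separate statistical analysis plan is announced. An unadjusted log-rank test placed between Kaplan-Meier estimates and an adjusted model can be read as description.

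Much of this stands:

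- No confirmatory claim is made for secondary outcomes, so no promised error rate is broken.
- Which p-value leads for a given endpoint can be left to the analysis plan.
- The ICC of 0.1 was assumed for the binary primary outcome, and the clustering of the comparison group is not described. The article does not exclude participating hospitals from the claims data.

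It does not remove the point. The log-rank test is named in the article without cluster adjustment, and a valid companion model does not make its p-value valid. A descriptive p-value with too small a variance still misdescribes the evidence. The case in which the problem disappears, with the same hospitals supplying both groups equally, is not a design the article sets out.

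A reader might infer three stronger things that the article does not support:

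- **That all descriptive secondary p-values ignore clustering.** The test behind them is not named, so this would be an inference.
- **That no cluster-aware analysis is planned for secondary outcomes.** One is.
- **That the error rate reaches 40%.** By the formula this needs DE 5.42, for example about 45 patients per ICU (1 + 44.2 × 0.1), or 37.4 per ICU with an assumed coefficient of variation of cluster size of about 0.5 (40.6%). Neither follows from the stated inputs.

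**Conclusion.** The point holds, conditionally and for the log-rank tests. As written, the plan would yield log-rank p-values whose variance ignores a clustering that the plan itself assumes.

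The size of about 29% (25 per ICU) to 36% (37.4 per ICU) rests on two assumptions: that ICC 0.1 carries over from weaning failure to the time-to-event endpoints, and that the comparison group is clustered like the intervention group. Relaxing the second gives about 19-30%. A lower ICC of 0.01-0.05 gives about 8-24%. Inflation is therefore likely, but the article does not fix its amount.

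The primary outcome, its model and its error rate are untouched. For the remaining secondary outcomes the point is only a request to say where the descriptive p-values come from.

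**What to change.** In the Final analysis section, or in the statistical analysis plan:

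1. Take between-group p-values and confidence intervals for time-to-event endpoints from the planned shared frailty model with a random effect for centre. Alternatively, replace the ordinary log-rank test with a version whose variance is clustered on ICU or hospital.
2. Keep the Kaplan-Meier curves as description.
3. For the other secondary outcomes, state that the descriptive p-values come from the planned mixed models.

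The cost is a change of wording. Data, recruitment and the primary analysis stay as they are, and the cluster-aware models are already planned. The downside is that some secondary p-values will look less favourable.
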